### Economic evaluation

Primary economic analysis will take a cost consequences analysis (CCA) approach, that is, we will estimate the additional cost associated with the introduction and use of (i) nurse-led computer-supported telephone triage, or (ii) GP-led telephone triage compared to usual care/practice in the management of patients requesting same-day consultations in primary care, and present the costs alongside the benefits (if any) identified in the trial. The CCA approach is regarded as a form of full economic evaluation
[51] even though findings are not specifically summarised into an incremental cost-effectiveness ratio. Given the expected consequences of the interventions being compared, for example, any change in the type or nature of primary care index or follow-up contacts or change in NHS resource use at a patient level, we see CCA as the most policy-relevant approach for the economic analysis as it provides decision-makers with information in a clear way and allows them to consider the issue of value for money in a context-specific manner. The primary economic analysis will estimate the mean costs of care associated with the primary outcome and triage (where used) for each of the trial arms for a four-week follow-up period.

Economic analysis will be undertaken from the perspective of the NHS and Personal Social Services (PSS), as for the current NICE reference case
[52]. The nurse- and GP-led triage systems being compared to usual care are expected to involve some organisational change and additional resource use. These intervention costs will be estimated using within-trial case report forms from each participating general/primary care practice, to identify the additional components of resource use, and to measure the additional resource use for each intervention, compared to usual care or practice. Within both) nurse-led computer-supported telephone triage and GP-led telephone triage there will be a cost associated with staff training and initial set-up. Training log sheets will be used to accurately capture the duration of all staff training associated with the trial by staff type. There will be capital costs associated with nurse-led computer-supported telephone triage (provided by Plain Healthcare), and these will be depreciated against the expected life of the capital investments. Finally, within nurse-led computer-supported telephone triage and GP-led telephone triage, there will be time spent by nurses and GPs respectively on triaging patients that will be captured by asking the clinician delivering triage to fill in a data collection instrument, the clinician form.

Trial outcomes will identify resource use for each participating patient (for example, nurse, GP, out-of-hours, A&E, WIC), and trial analysis will report differences between such resource use for each arm of the trial over a four-week follow-up period. Data on resource use (participant level) will be combined with credible unit cost data from published and/or NHS sources
[53,54] to estimate the mean cost (as previously discussed) for each arm of the trial, and mean cost over the four weeks from (and including) the index consultation. Methods used for collection of resource use data, other than against primary trial outcomes, were explored and refined in the pilot and feasibility phase of the research, to ensure methods were feasible and acceptable to participating primary care practices.

All data sources and assumptions used in the economic analysis will be clearly presented. Parameter and structural uncertainty will be addressed using extensive sensitivity analyses (one-way, multi-way, scenario analyses, and probabilistic/bootstrapping approaches). Analysis will be undertaken to investigate health-related quality-of-life (four weeks after the index consultation) using the EQ-5D, however, in the absence of a baseline quality of life measure, such analysis will be exploratory. Further exploratory analysis will be undertaken to investigate the impact on cost of using micro-level costing for follow-up appointments. Such micro-level costs will be informed by obtaining duration data as described (Secondary outcomes). Results presented from the economic evaluation will allow decision makers (macro-, meso- and micro-level) to consider the relative merits of the interventions in a policy-relevant way.

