### Primary outcome

The primary outcome measure is the number of healthcare contacts taking place in the four-week period following the index same-day consultation request. The number of contacts will include the initial clinical assessment contact, and will thus include the triage contact in the two intervention conditions. The total number of contacts per 1,000 patients requesting same-day consultations in each of the trial conditions will be derived from numbers of GP, practice nurse, GP out-of-hours, A&E, and (although they may not impact significantly on GP workload
[36]) NHS WIC attendances. Data collection, capturing information on timing (am/pm), and type (face-to-face, telephone, home visit, GP out-of-hours, A&E and WIC attendance) of primary care contacts in all trial practices will take place as part of a note review occurring at least twelve weeks after the index consultation request with data extracted from the primary care medical record. We will count the day of the index request as day 1 (same day), and include the following 28-day period (day 1 to day 28 inclusive) starting from the day following the consultation request.

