We will survey patients who have requested same-day consultations in each of the three trial conditions using a modified version of the national survey instrument. Whilst the national survey explores patients’ experiences of care in the past 6 months, we will modify relevant questions to focus on the participants’ recent experiences of care following their same-day consultation request.

The responsiveness of the consultation management system will be assessed using patient reports of care received (for example, how quickly care was provided and overall satisfaction) and their evaluations (using a 5-point Likert scale)
[41,42] of the timeliness and convenience of the response
[43] to the original same-day consultation request incorporated into the follow-up questionnaire.

For patient safety, deaths within 7 days of the same-day consultation request (from practice records), and attendance at A&E within four weeks and number and length of stay of emergency (unplanned, that is, admission with no evidence of prior planning of that admission within a one-day period at notes review) hospital admissions within 7 days of the index consultation (from primary care records examined twelve weeks after the same-day consultation request).

Patient health status will be assessed by the widely used EuroQol Group 5-Dimension Self-Report Questionnaire (EQ-5D) measure
[44] incorporated into the follow-up questionnaire, along with a question on problem resolution
[27,28] (5-point Likert scale).

For descriptive data, we will collect patient-level (for example, on age and gender) and practice-level (for example, on practice size, staffing and deprivation index) data. Two approaches to defining patient casemix will be adopted: (i) we will record morbidity on the basis of the principal systems involved (after
[28,29]), allowing for clinicians to record up to three systems in respect of each consultation; (ii) an 8-point score will be used to define the complexity of the case (after Howie
[45]) with each consultation being defined as having substantial (2 points), attributable (1 point) or no content (0 points) in respect of each of four domains, namely, physical, social, psychological or other (for example, administrative) components to the consultation.

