The influence of practice-level characteristics (for example, deprivation, location and list size) on the primary outcome will be investigated using interaction terms. Although the power to detect moderate subgroup interactions will be low, we are primarily interested in investigating the possibility of large interactions, which are qualitative (the direction of treatment effects varies between subgroups) rather than quantitative (the magnitude of the treatment effect varies between subgroups, but not the direction). This subgroup analysis will be restricted to the primary outcome.

Sensitivity analyses will be conducted to investigate the potential impact of missing data on the primary outcome only. These will include making different assumptions such as best-case scenarios (for example, assuming a patient who does not consent to a case notes review has zero healthcare contacts in the four-week period following the initial telephone call requesting a same-day appointment), as well as multiple imputation models. Available demographic characteristics (depending on whether questionnaire is completed) of patients who consent to the case notes review will be compared to those who do not.

The primary economic analysis will estimate the mean cost of care across each of the trial arms, to include triage (where used) and the items in the primary outcome. Economic analyses will be based on a micro-level costing estimate for the triage intervention, and the use of published unit cost data for other elements of resource use. Estimates of the cost associated with triage interventions will be based on incremental costs when compared to usual care, with any capital costs and/or training costs depreciated/spread over an appropriate time period in the primary analyses (with other time horizons for these costs explored in sensitivity analyses).

The economic evaluation will present between group comparisons of costs using the regression-based statistical methods described above. Mean participant-level cost estimates for the triage interventions will be presented, with 95% CI. Although cost data often does not follow a normal distribution and parametric tests are therefore not appropriate, if a sample has a large number of observations as in this case (circa 18,000), incorporating central limit theorem implies parametric tests are appropriate and may be used
[9].

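### The economic analysis claims an NHS and PSS reference-case perspective, but its primary four-week cost leaves out inpatient care and no described instrument measures PSS use

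*Protocol article*

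**What the plan says.** The perspective is set in Economic evaluation: "Economic analysis will be undertaken from the perspective of the NHS and Personal Social Services (PSS"), which the section aligns with the NICE reference case.

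The same section fixes what the main analysis costs: "The primary economic analysis will estimate the mean costs of care associated with the primary outcome and triage (where used"), and the horizon: "for each of the trial arms for a four-week follow-up period". Statistical analysis repeats the scope, saying that the mean cost is "to include triage (where used) and the items in the primary outcome".

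Primary outcome lists those items. The count is "derived from numbers of GP, practice nurse, GP out-of-hours, A&E, and" walk-in centre attendances. Hospital admission is not among them.

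Emergency admissions and their length of stay appear under Secondary outcomes as a patient-safety measure, limited to "hospital admissions within 7 days of the index consultation". In the same sentence, A&E attendance is followed for four weeks.

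The Case note review section says that reviewers record hospital admissions along with other contacts, at least twelve weeks after the request. It gives no time limit for the admissions to be recorded.

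**The concern.** The perspective tells a reader whose costs the result covers. An NHS and PSS perspective covers inpatient care and social services as well as primary care. The primary cost defined here covers neither. If the plan is followed as written, the result will carry a label that its data do not support.

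The inpatient gap matters more than the PSS gap. Both interventions manage by telephone some patients who would otherwise have been seen in person. The Background reports a review that raised the possibility of delay in definitive care, and one triage study with a 200% rise in A&E attendance on small numbers. The section on minimising delays to care treats avoiding delay as essential. If delay did lead to admission, that is where its cost would fall, and this component is outside the primary cost.

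**Working it through.** No figure in the plan is in dispute, so the check sets the stated perspective beside the costed items and the instruments.

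**1. Components implied by the perspective, against the plan**

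- Triage, training, set-up and capital: costed, using practice forms, training logs and the clinician form (Economic evaluation).
- GP, practice nurse, out-of-hours, A&E and walk-in centre contacts: costed over four weeks (Primary outcome; Economic evaluation; Statistical analysis).
- Inpatient care: not in the primary cost. It is defined only as a safety outcome to day 7 (Secondary outcomes).
- Personal Social Services: no measure is named. The clinician form covers the consultation itself, the questionnaire is described as covering satisfaction and health status, and the note review covers healthcare contacts and admissions.

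Elsewhere the article describes a narrower scope. The Abstract speaks of cost to the NHS, and Secondary outcomes describes the resource measure as NHS primary care use. The perspective sentence is the one that does not fit.

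**2. Windows**

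- Costing horizon and A&E attendance: 28 days.
- Defined emergency-admission outcome: 7 days.
- Coverage: 7 / 28 = 25%. Days 8 to 28, 21 / 28 = 75% of the costed period, have no defined admission outcome.

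For example, a patient who attends A&E on day 10 and is admitted contributes one A&E contact to the primary cost and one A&E attendance to the safety data. The admission and its length of stay enter neither the primary cost nor the defined admission outcome.

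**3. Effect on the cost comparison**

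Write the full difference between two arms as D(full) = D(primary) + D(inpatient) + D(PSS). The plan estimates D(primary). For emergency admissions, D(inpatient) is roughly (difference in admissions per patient) × (cost per admission).

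- If the arms have the same inpatient and PSS use, the difference is unaffected and only the level of cost is too low.
- If one arm has more admissions, its relative cost is understated by D(inpatient).
- If it has fewer, its relative cost is overstated.

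The article gives neither an admission rate nor a unit cost, so D(inpatient) has no documented value or sign.

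**The case against.** Several points on the other side are sound.

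- **The scope is stated openly.** Economic evaluation names the costed items just before it names the perspective, so a careful reader can see the limits.
- **The format is cost-consequences.** Outcomes are shown beside costs, so admissions and length of stay can appear there. As defined, however, they would appear only to day 7.
- **There is room for more.** The patient-level resource list is given as examples, resource data beyond the primary outcome are mentioned, and extensive scenario and structural sensitivity analyses are promised. A full statistics and health economics plan exists but is not shown. Any of these may bring in admission costs. None changes the primary cost that the article fixes, or the perspective that it attaches to it.
- **A seven-day window is defensible.** It favours events attributable to the index request, and a longer window admits unrelated admissions.
- **PSS use over four weeks may be small.** Nothing in the article suggests that it would differ between arms.

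A reader might also infer stronger claims that the article does not support.

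- **That admissions are recorded only to day 7.** Seven days is the limit of the defined outcome. The note review records admissions with no stated limit, so later ones may already be extracted.
- **That a later admission through A&E leaves no safety trace.** A&E attendance to four weeks is itself a safety outcome.
- **That the omission could cancel or reverse the cost of the 0.36-contact target difference.** That target is an increase under nurse triage: 1.38 - 1.02 = 0.36. Extra admissions in that arm would add to its excess cost. Offsetting is conceivable for GP triage, where a 30% reduction is assumed (0.30 × 1.02 = 0.306 fewer contacts if applied to the usual-care mean). Even there, the primary cost also contains training, set-up and triage time, and the article has no admission figures with which to test it.
- **That the Background ranks delay as the main risk.** It reports a possibility, and also says that telephone consultation appears safe and effective.

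**Conclusion.** The point holds as a mismatch within the article. The stated perspective is the NHS and PSS reference case, while the primary cost is triage plus primary care, out-of-hours, A&E and walk-in centre contacts over four weeks. Inpatient care is outside that cost and is defined as an outcome for only 25% of the costed period. PSS use is not named in any described instrument.

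The consequence is limited but real. The primary cost comparison cannot show a difference in inpatient care and would understate the cost of an arm that moves care into hospital. How large this would be, and which arm it would favour, cannot be calculated from the article. The conclusion rests on the article's own definitions of perspective, costed items and windows. It does not assume that admissions will differ between arms. The primary clinical outcome and its analysis are unaffected.

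**What to change.** 1. Restate the primary perspective as the cost of triage plus primary care, out-of-hours, A&E and walk-in centre contacts over 28 days, and drop the claim to the NHS and PSS reference case.
2. From the existing note review, take emergency admissions and length of stay to day 28. Add their cost in a named sensitivity analysis and report them in the cost-consequences table. Keep day 7 as the primary safety window.

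The cost is a change of wording and, if the extraction form currently stops at day 7, a wider date range on a review that already takes place at twelve weeks or later. Recruitment and patient contact are unaffected. The downside is that some unrelated admissions will add noise to the 28-day figures, which is why the day 7 outcome is kept.

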### Data collection

#### Clinician data collection forms

Clinicians will complete a short data collection form (clinician form) at the time of the initial consultation following a patient’s same-day request (triage or usual care contact). This form captures details of the consultation including which health professional undertook the consultation, whether the patient did not attend, case-mix (see Secondary outcomes, Descriptive data), treatment and management options chosen (for example, ordering of tests, recommending subsequent appointment or referral), start and end time of the consultation and the patient’s response to the initial verbal consent to note review, which the clinician asks for at the end of the consultation.

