### Interventions

#### GP-led telephone triage

We will use components of the Stour Access System to deliver GP-telephone triage
[30] as designed in 2000 by a four-partner teaching practice in Christchurch, Dorset, UK. A core element of the intervention is the use of the GP to undertake triage (as opposed to other non-medical members of the clinical team) for patients registered with their practice. Whilst Stour’s general model is that all appointment requests are triaged, in this study we focus only on those patients seeking same day consultations.

Stated success factors of the Stour GP-led triage system
[30] include patients who did not attend appointments (DNAs) reduced to almost zero (from estimated national average of 6.5% to 7.7%
[31,32]) and one-third of patients being dealt with over the phone without needing to see a member of the practice team. However, these claims are not yet supported by any other published evidence.

The triage component of the Stour Access system operates as follows. Once the receptionist has established that the patient is requesting a same-day appointment, the patient is asked to leave a contact number with the receptionist and is advised that the GP will call them back within around 1 to 2 hours. This timescale (for both the GP-led and nurse-led arm) is flexible, so as to optimise prioritisation. The GP discusses the complaint with the patient and triages them to the most appropriate person, such as a nurse, or books a face-to-face appointment with the GP, or provides advice on the telephone. An appointment slot with the appropriate clinician is booked by the GP - the patient is not referred back to the receptionist for this. An integral part of the Stour system is that patients can book directly with the nurse or other non-GP members of the primary care team and can access a walk-in nurse clinic where the practice offers this.

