### Secondary outcomes

1.Descriptive study of patient flow: we will describe the management and interim and final disposition of patients in the working day in which they request a same-day consultation, up to the point of final contact within that working day, for each of the trial conditions.

2.Primary care NHS resource use: we will capture NHS primary care resource use by collecting data on the number of contacts resulting for patients in the three trial conditions, as for primary outcome, over a four-week follow-up. We will collect actual consultation length for initial triage and usual care (face-to-face or telephone) consultations (described below). We will estimate the length of subsequent consultations, for same-day and four-week follow-up periods based on the recorded start and end times of a sample of consultations captured over two randomly selected days in each practice during the patient recruitment period. For costs, see health economic evaluation below. Non-attendance rates for allocated appointments in the month following the same-day request will be described and compared between trial conditions using data extracted at practice record review.

3.Patient experience of care, safety, and health status: these patient-reported outcomes will be collected by postal questionnaire four weeks following the request for a same-day consultation. This time frame has been selected to capture a period for optimal recall, which may encompass events and experiences that could feasibly be linked to the initial reason for contacting the GP practice for a same-day consultation.

For patient experience of care, whilst this study focuses on patients’ experiences of an episode of care delivered following a same-day consultation request, and possibly involving multiple healthcare contacts during the course of the index day, currently available survey instruments suitable for use in a UK setting have focused on the evaluation of individual consultations
[37,38] or aggregate (practice-based) care. No validated instruments for assessing the patient’s experience of an overall episode of care following such a request, and possibly involving multiple interactions, have been identified. We propose to use a modification of the new national GP patient survey instrument for the purposes of monitoring patient experiences of care in this study. This study team is in a unique position
[39,40] to have early access to this instrument for research purposes.

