#### Case note review

Research staff will undertake a review of case notes of patients who have consented to have their notes reviewed (see below for further details of procedure for obtaining informed consent). This will take place a minimum of twelve weeks after their initial same day consultation. The case note review will be undertaken in the relevant GP surgery and patients’ notes will not leave the surgery. The purpose of the review will be to record information on the number and type of healthcare contacts including casualty contacts and hospital admissions, and length of consultations where this information is available. Laptops or memory sticks (encrypted as per NHS security requirements) will be used by researchers to record encrypted data in the research database. A standardised process will be adopted when searching notes.

Although it is not possible to blind research staff to the trial arm that a practice has been allocated due to the cluster design, a small validation study will be undertaken to explore the impact of lack of blinding on the outcome assessment process. During the feasibility study, a small sample of notes (30 from one practice) was independently examined by the four trial researchers, and the relevant data extracted. The inter-rater reliability of the data extraction process was assessed, and any divergence between assessors documented and resolved with a view to developing standardised procedures to guide the review process in the main trial.

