### Informed consent

Practice recruitment arrangements are described previously. All patients requesting same-day consultations over the five-week recruitment period in the study practices will be eligible for inclusion in the study (subject to the age limits specified above).

When patients call the practice seeking a same-day consultation the receptionist will advise them (or the guardian of children aged less than 12 years) of the current practice consultation arrangements. Once it has been ascertained that the patient does not require urgent or emergency care, the receptionist will explain briefly that a trial is taking place and advise the patient that the practice would appreciate them participating in a questionnaire survey, which will be sent to them for their consideration within around four weeks. The consulting (triage/usual care) clinician will reiterate that patients may be sent a questionnaire to ask their opinion of the triage system/existing consulting arrangements, and will ask patients at the end of the clinical interaction whether they would be agreeable to a researcher reviewing their notes in twelve weeks time. The patient’s verbal consent will be noted on a data collection form. Four weeks later the practice will send patients an information sheet describing the study, a questionnaire and a prepaid return envelope. Participants may opt out of the notes review on the last page of the questionnaire, should they wish to do so at that stage. A name with contact details will be provided should patients require any further information and those who do not wish to complete a questionnaire will be encouraged to return their blank questionnaire in the prepaid envelope, and they will receive no further contact in relation to the study. Those who do not respond to the questionnaire will be sent a second and third mail-out of the questionnaire and information sheet two and four weeks later.

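### Comparing non-attendance from the consented record review probably under-counts missed first appointments in usual care, to the disadvantage of the triage arms, although the clinician form already records them

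*Protocol article*

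**What the plan says.** **Source of the outcome.** Under Secondary outcomes (item 2), non-attendance rates for appointments allocated in the month after the request "will be described and compared between trial conditions using data extracted at practice record review". No other source is named for this outcome.

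**Who is in the source.** Case note review: "Research staff will undertake a review of case notes of patients who have consented to have their notes reviewed".

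**When consent is asked.** Clinician data collection forms describes the initial "verbal consent to note review, which the clinician asks for at the end of the consultation". Informed consent agrees: the consulting clinician "will ask patients at the end of the clinical interaction whether they would be agreeable to a researcher reviewing their notes in twelve weeks time". Patient recruitment gives the same timing.

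**What the form holds.** The clinician form is completed for the first contact after the request, whether triage or usual care. "This form captures details of the consultation including which health professional undertook the consultation, whether the patient did not attend".

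**Other routes into the review.** Sample size says the pilot led to verbal consent being included alongside the written route. Feasibility (under Methods/design) still puts written consent to record review in the postal pack. Informed consent and Questionnaires give the questionnaire an opt-out role only. Confidentiality treats consent as not having opted out.

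**Why the outcome is there.** The section on GP-led telephone triage reports a claim that missed appointments are "reduced to almost zero (from estimated national average of 6.5% to 7.7" per cent). It adds that such claims lack other published support.

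**The concern.** Whether a missed first appointment is counted depends on whether the patient enters the review, and the chance of entering depends on having attended. That dependence differs by arm.

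In a triage arm the first contact is the call. A patient can agree to note review on the call, miss the appointment booked from it, and be counted. In usual care the first contact can be the appointment. A patient who misses it is not there to be asked, so the miss is less likely to reach the data meant to count it.

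This is selection on the outcome itself, so neither more patients nor covariate adjustment removes it. It lowers the observed usual-care rate. It therefore runs against both triage arms and could mask the reduction in missed appointments claimed for the GP-led system.

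**Working it through.** **1. The protocol's own figure.** No expected difference or power is stated for non-attendance. The related figure is review coverage. With 30% not responding to the written request and 10% of responders declining, 0.70 × 0.90 = 0.63, which reproduces the stated 63%. The revised 78% is given without components and is used as stated.

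**2. Order of events.**

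| | Triage arms | Usual care, appointment as first contact |
|---|---|---|
| Request flagged by receptionist | yes | yes |
| Verbal consent asked | on the call | at the end of the appointment |
| Appointment that can be missed | after consent is asked | before consent is asked |
| Missed appointment counted in review | as often as an attended one | only if the patient enters by another route |

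**3. Observed rate at the usual-care first appointment.** Let p be the true miss rate, c the review coverage of attenders and w the review coverage of non-attenders.

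Observed rate = p·w / [p·w + (1 − p)·c]

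Inputs: p = 6.5% and 7.7%, the national averages in the GP-led triage section, assumed to apply to same-day appointments; c = 0.78, the overall revised figure, assumed to apply to attenders; w is an assumption and is varied.

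| w | Reading | p = 6.5% | p = 7.7% |
|---|---|---|---|
| 0 | verbal consent is the only route | 0% | 0% |
| 0.30 | partial entry by another route | 2.6% | 3.1% |
| 0.63 | entry at the original written-consent rate | 5.3% | 6.3% |
| 0.78 | pure opt-out, no difference in coverage | 6.5% | 7.7% |

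For example, with p = 0.065 and w = 0.63: 0.04095 / (0.04095 + 0.7293) = 5.3%. At w = 0.63 the shortfall is about 1.2 to 1.4 points. For an appointment booked from a triage call, consent is asked beforehand, so w = c and the formula returns p.

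**4. All appointments in the month.** Add f later appointments per patient with the same miss rate (assumption: f = 0.25 to 1).

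Observed rate = [p·w·(1 + f·p) + (1 − p)·c·f·p] / {[p·w + (1 − p)·c]·(1 + f)}

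- w = 0 reduces to f·p / (1 + f): from 0.25 × 0.065 / 1.25 = 1.3% to 1 × 0.077 / 2 = 3.9%, against a true 6.5% to 7.7%.
- w = 0.63 gives 5.6% (p = 6.5%, f = 0.25) to 7.0% (p = 7.7%, f = 1). The shortfall is about 0.6 to 1.1 points.

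Steps 3 and 4 assume that every usual-care first contact is an appointment that can be missed. Where it is not, the shortfall is smaller.

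**The case against.** A reader might infer that missed first appointments vanish altogether from usual care, and put a large figure on it. Take a 5% miss rate at the index-day appointment in every arm, 0.3 to 0.5 later appointments per patient missed at 7%, and 50% to 67% of triaged patients booked in. Usual care would then show 1.6% to 2.3% against 5.6% to 6.0% under triage. The documents do not support this as the expected result, for three reasons.

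- It needs w = 0. Patients are flagged when they call, and Feasibility has the survey sent to those identified for the trial with a written consent section. Sample size says verbal consent was included, not that it replaced the written route. Confidentiality reads as opt-out. A non-attender may therefore enter the review.
- It needs every usual-care first contact to be a missable appointment. Secondary outcomes allows telephone first contacts in usual care. The eligibility rule admits practices that triage up to 75% of same-day requests. Where usual care telephones first, consent is asked as early as under triage.
- Apart from the national non-attendance average, its inputs have no source in the protocol.

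These points limit the size but do not remove the mechanism. Only a pure opt-out with equal coverage does that. Such a reading sits badly with Case note review, and with the sensitivity analyses under Statistical analysis, which provide for patients who do not consent to note review.

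Three further points are fair. First, an unanswered triage call is lost from the review in the same way as a missed usual-care appointment; what the triage arms count is the appointment missed after the call. Second, that the practice record review in Secondary outcomes is the consented case note review is an inference, though no other record review is described. Third, a full analysis plan exists and is not shown, and it may use the form. The article nevertheless names a source, and following it as written gives the uneven comparison.

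**Conclusion.** The concern holds in a limited form. As written, the non-attendance comparison probably under-counts missed first appointments in usual care relative to appointments missed after a triage call, and the error runs against the triage arms.

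Its size cannot be fixed from the protocol, because the passages on how a patient enters the review conflict. With a true rate of 6.5% to 7.7% and 78% coverage of attenders, the observed usual-care first-appointment rate lies anywhere from 0% (verbal consent only), through 5.3% to 6.3% (63% of non-attenders reviewed), to the true rate (pure opt-out). Telephone or triage first contacts in usual care dilute the effect by an amount the protocol does not give. Missed later appointments of reviewed patients are counted in all arms.

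This is a secondary outcome with no stated power, and the primary outcome and sample size are untouched. The change is worth making because it is cheap and removes the dependence on how the consent passages are read.

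**What to change.** 1. In Secondary outcomes, take non-attendance at the first allocated contact from the clinician form, for every flagged patient in all three arms.
2. Before doing so, confirm that the approved consent arrangements allow form data to be used for patients who were never asked about note review. The protocol does not say.
3. Use the record review for appointments after the first contact, and do not base the arm comparison on it alone.
4. Report unreached triage calls separately from missed appointments.
5. Reconcile Sample size, Feasibility, Case note review, Informed consent and Confidentiality so that they state one rule for how a patient who missed the first contact enters the review.

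Cost: a change of wording in the outcome definition and the analysis plan, the check in item 2, and the work of combining two sources. The form already collects the item.
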